#### Pre-admission clinical and service use analysis

We will report the clinical and service use variables in online supplemental table 2 for the 6 months before hospital admission and compare variables between those who had a pre-admission community C(E)TR and those who did not. This will also be implemented using standard statistical comparisons for categorical (χ^2^) and continuous variables (t-test or Kruskal-Wallis).

#### Time-to-event analysis

Time-to-discharge (length of hospital admission) will be analysed using the Kaplan-Meier estimator.^19^ A Cox’s proportional hazards model will be used to estimate the HR for discharge,^20^ comparing those who received a C(E)TR to those who did not receive a C(E)TR for a follow-up period of 6 months after admission. This analysis will be adjusted for C(E)TR status prior to admission, age at admission, sex, ethnicity and relevant diagnosis at admission (intellectual disability with/without autism, or autism alone). Patients who die within 6 months of admission will be censored at the date of death, and patients who remain in hospital will be censored at the end of the 6 months.

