## Abstract

**Abstract:**

**Introduction:**

Care (Education) and Treatment Reviews (C(E)TRs) are intended to reduce unnecessary psychiatric hospital admission and length of stay for people with intellectual disability and autistic people. The use and impact of C(E)TRs have not been systematically evaluated since their introduction in England in 2015. The aims of this study are to describe the demographic and clinical profiles of people who receive a community C(E)TR and to investigate their effects on admission, length of hospital stay and clinical and functional change.

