## Introduction

 Reducing unnecessary psychiatric hospital admissions and length of hospital stay for people with intellectual disability and autistic people has been a focus of English national health policy since the scandal of abuse and neglect of patients at Winterbourne View Hospital in 2011.^1^ The Transforming Care programme was established to improve community health and social care for people with intellectual disability and autistic people and to reduce what had generally been considered to be an over-reliance on inpatient psychiatric services.^2^ A key element of Transforming Care has been the introduction of Care (Education) and Treatment Reviews (C(E)TRs), person-centred review meetings that aim to ensure the right support is provided.^3^ A community C(E)TR should be convened when a person with intellectual disability or an autistic person living in the community is considered at high risk of admission to a psychiatric hospital, either because of mental ill-health or because of an escalation in behaviours that challenge. C(E)TRs are chaired by a health commissioner and include an independent clinical expert and an expert-by-experience, often a family carer of a person with intellectual disability or an autistic person. This panel gathers information from the individual, their families and carers, and professionals, and produces a report and action plan following the C(E)TR with recommendations (eg, input from specialist professionals or health teams, provision of additional care, use of respite services) that can enable the person to remain living safely in the community. Where admission to hospital is considered necessary, the C(E)TR panel will define the purpose of the admission and encourage early discharge planning in order to minimise the length of the hospital stay. Inpatient C(E)TRs are convened at various points of a hospital admission; the current project investigates only C(E)TRs that are held in the community.

Little formal research has been carried out on community C(E)TRs, such as who receives them and when, and how C(E)TRs may influence health service use, including admission to hospital. By understanding the demographic and clinical profile of patients who do, and do not, have a community C(E)TR, it may be possible to develop targeted interventions to improve access to community C(E)TRs and ensure the potential benefits are available to everyone.

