## Methods and analysis

### Study setting

Data will be obtained from the South London and Maudsley (SLaM) NHS Foundation Trust. SLaM is one of the largest providers of secondary mental healthcare in Europe, with a diverse catchment area of approximately 1.3 million people who live in the south London boroughs of Lambeth, Southwark, Lewisham and Croydon. Mental health services provided by SLaM include specialist teams for children and adolescents with mental illness and/or neurodevelopmental conditions, community teams for adults, including specialist teams for those with intellectual disability, and mainstream and specialist inpatient wards across different sites. The Trust has implemented a full EHR since 2006, and the SLaM NIHR Maudsley Biomedical Research Centre Case Register contains the clinical records of >5 00 000 patients.^4 5^ Unless otherwise stated, data will be extracted up to an end date of 31 December 2024. The protocol for this study was finalised in July 2025. Data extraction is anticipated to be complete by September 2025 and data analysis by December 2025.

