### Study eligibility criteria

Individuals of any age with a diagnosis of intellectual disability (ICD-10 code F7x) or autism (ICD-10 code F84) will be identified using diagnostic information entered into structured fields or in the free text record using the NLP diagnosis application. Participants must have a recorded diagnosis of intellectual disability and/or autism. Eligible participants must have received an episode of care from a community mental health service provided by SLaM for at least one continuous year between 1 January 2015 and 31 December 2023 to ensure that sufficient data are held in the record. All eligible episodes of care will be included, including those individuals with more than one period of community care of at least 1 year during this timeframe.

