### Matching a control group

We will match between one and five controls, who will not have a community C(E)TR, per patient who has a C(E)TR. Eligibility will be a diagnosis of intellectual disability or autism and having received a continuous period of community care within SLaM services for at least a year between 1 January 2015 and 31 December 2023. Matching will be based on age (±3 years), sex (male/female) and diagnosis (intellectual disability with/without autism, or autism without intellectual disability). Controls should be under an active episode of community care and not be an inpatient on the index date of their matched case. They must also have been under SLaM services for a similar total duration of their matched case (±2 years). Matching with replacement will be applied to ensure every case has an appropriate match according to these criteria. A pseudo-index date for each control will be assigned and will be the same as the index date of their matched case.

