### Identifying cases and controls

Using the review of clinical records of eligible patients previously described, we will measure whether each patient had a community C(E)TR within 6 months prior to their psychiatric hospital admission. We will form two groups: those who had a pre-admission community C(E)TR, and those who did not.

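### Sub-study 2 compares unmatched admissions from 2015 onward without adjusting for admission date, so calendar time can confound the C(E)TR association if both uptake and outcomes trended

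*Protocol article*

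**What the plan says.** The abstract states that C(E)TRs "have not been systematically evaluated since their introduction in England in 2015". Under Study eligibility criteria, participants need community care "for at least one continuous year between 1 January 2015 and 31 December 2023", and under Study setting "data will be extracted up to an end date of 31 December 2024". The window therefore opens in the introduction year and runs for about a decade.

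The Introduction presents C(E)TRs as one element of Transforming Care, a programme set up in part "to reduce what had generally been considered to be an over-reliance on inpatient psychiatric services". It also says: "Reducing unnecessary psychiatric hospital admissions and length of hospital stay for people with intellectual disability and autistic people has been a focus" of national policy, dating this from 2011. Length of stay is the primary outcome of sub-study 2 in Table 1.

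Sub-study 2 does not match. Under Identifying cases and controls: "We will form two groups: those who had a pre-admission community C(E)TR, and those who did not". The Time-to-event analysis section then gives a closed list for the Cox model, which is "adjusted for C(E)TR status prior to admission, age at admission, sex, ethnicity and relevant diagnosis at admission". The HoNOS change model, described under Improvement in clinical and social functioning during hospital admission, has C(E)TR group, baseline HoNOS, age, sex and ethnicity. Neither list includes admission year or period, and no sensitivity analysis for sub-study 2 addresses it.

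Sub-study 1 differs. Under Matching a control group, each control's pseudo-index date "will be the same as the index date of their matched case".

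**The concern.** A review introduced in 2015 may well have become more common over the following years. If so, patients with a pre-admission C(E)TR were admitted later, on average, than those without. Over the same years other elements of national policy were directed at the outcome itself. Calendar time could then be related to both exposure and outcome, and the models as listed leave it uncontrolled.

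At stake are the discharge HR and the HoNOS coefficient. Part of either could reflect a change in inpatient care over the decade rather than anything associated with the C(E)TR. The plan recognises a related problem: Inclusion and exclusion criteria removes people without six months under a community team, partly because they may not have had the chance of a C(E)TR. Nothing equivalent deals with when in the roll-out the admission fell.

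**Working it through.** **Inputs from the article.** Eligible care runs from 2015 to 2023, nine years. Follow-up for discharge is six months. The groups are an unmatched split by C(E)TR in the six months before admission. The covariate lists are as above. The article gives no HR, event count, C(E)TR uptake by year or trend in stay, so there is no stated figure to reproduce.

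**Inputs assumed.** Admissions are spread evenly over nine years. Uptake rises linearly from p0 to p1. The discharge rate changes by a proportion g each year. Stays are exponential with a median of 60 days in 2015. The true HR is 1.

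**Step 1: gap in mean admission date, exposed minus unexposed.**

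D = slope × Var(T) / [p̄(1 − p̄)], with slope = (p1 − p0)/9, Var(T) = 9²/12 = 6.75 and p̄ = (p0 + p1)/2.

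- 0% to 30%: 0.0333 × 6.75 / (0.15 × 0.85) = 0.225/0.1275 = 1.76 years
- 0% to 50%: 0.0556 × 6.75 / (0.25 × 0.75) = 0.375/0.1875 = 2.00 years
- 5% to 15%: 0.0111 × 6.75 / (0.10 × 0.90) = 0.075/0.09 = 0.83 years
- Flat uptake: slope 0, so D = 0

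**Step 2: HR without a year term.** To a good approximation HR ≈ (1 + g)^D. Solving the large-sample Cox score equation numerically, with censoring at 182 days, agrees to within about 0.002.

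| Uptake | g = −5% | g = 0 | g = +3% | g = +5% | g = +10% |
|---|---|---|---|---|---|
| 0% to 30% | 0.91-0.92 | 1.00 | 1.05 | 1.09 | 1.18 |
| 0% to 50% | 0.90 | 1.00 | 1.06 | 1.10 | 1.21 |
| 5% to 15% | 0.96 | 1.00 | 1.03 | 1.04 | 1.08 |
| Flat | 1.00 | 1.00 | 1.00 | 1.00 | 1.00 |

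For example, 1.05^1.76 = 1.09 and 1.10^2.00 = 1.21. Compounded over nine years, 3%, 5% and 10% a year mean a discharge rate 1.30, 1.55 and 2.36 times its starting value, so the last column is a strong assumption.

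**Step 3: separate simulation.** With 60,000 admissions per run and total changes in discharge rate of 0.67, 1.5 and 2.0 over eight yearly steps, the HR was 0.93, 1.08 and 1.12 for uptake from 5% to 20%, and 0.91, 1.11 and 1.22 for uptake from 0% to 40%. Stratifying by admission year gave 0.98 to 1.03 in every run, which is 1 within simulation noise.

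**Step 4: early plateau.** If uptake reaches 20% within two years and then stays flat, the HR is about 1.02, 1.03 and 1.06 for 3%, 5% and 10% a year. If it does so within one year, it is about 1.01, 1.02 and 1.03.

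Bias therefore needs both a change in uptake and a trend in stay, and with rising uptake its sign follows the trend. The same reasoning applies to HoNOS change, but the article offers nothing on which to base a trend there, so no figure is attached.

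**The case against.** The strongest reply is that the article shows neither ingredient. It says the number of C(E)TR recipients is unknown and gives no uptake by year. It dates the policy focus on length of stay from 2011, before the window opens, and reports no trend in stay during it. With low, flat or early-plateauing uptake the bias is small or nil. This stands. A reader might infer that early admissions do load the comparison group, or that the C(E)TR will look better than it is. The documents support neither as fact: the first is a plausible inference from a 2015 introduction, and lengthening stays would reverse the second.

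A reader might also infer that many comparison patients were admitted before C(E)TRs existed. The article gives the introduction only as 2015, with no month. It also requires a continuous year of care within a window starting in January 2015. If that year precedes admission, which the article does not fix, the earliest admissions fall around January 2016 with a look-back from mid-2015. At most the earliest admissions are affected. Nor does the concern depend on them: with the whole first year dropped, a 5% yearly trend still gives about 1.04-1.07 across uptake patterns of 5-20%, 2-30% and 0-40%.

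Finally, sub-study 2 is worded as comparison and association; causal modelling is claimed only for sub-study 1. That softens the consequence, but a confounded association is still hard to interpret. A statistical analysis plan may exist, but the article lists both adjustment sets explicitly, so this is a stated choice and not a detail lost in condensing.

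**Conclusion.** The concern holds in conditional form. The two models as listed leave calendar time uncontrolled in a comparison that spans the roll-out of the exposure, whereas sub-study 1 controls it by design. Whether this biases the results, by how much and in which direction cannot be told from the article.

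Under the assumed linear roll-outs, the HR for length of stay moves from 1 to roughly 1.03-1.10 for yearly rises of 3% to 5% in the discharge rate, to 1.08-1.21 for a rise of 10%, and to about 0.90-0.92 for a yearly fall of 5% under the steeper uptake. With flat uptake or no trend it stays at about 1.0. These figures rest entirely on assumed inputs and cover length of stay only. The change is worth making because it is cheap and removes a bias that may be similar in size to a modest real association.

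**What to change.** - Add admission year to the Cox model, as a spline, as multi-year bands, or as strata by band. Add the same term to the HoNOS regression.
- Report the number and proportion of admissions with a pre-admission C(E)TR by admission year, so readers can see whether uptake changed.
- Optionally, as a sensitivity analysis, exclude admissions whose six-month look-back begins before a C(E)TR introduction date fixed in advance. This date should not be the first C(E)TR found in the record, which would be a data-dependent cut. Restriction alone does not replace the year term.

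Admission date is already the index date of sub-study 2, so no new data are needed. The cost is a few degrees of freedom, plus some loss of information if a band holds few exposed patients. For that reason bands or a spline are preferable to single-year strata.

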#### Sub-study 1: community cohort

Population, Intervention, Comparison and Outcome (PICO) framework (table 1).

**Table 1 T1:** Population, Intervention, Comparison and Outcome framework for sub-studies 1 and 2

	Sub-study 1	Sub-study 2
Population	People of any age with a recorded diagnosis of intellectual disability (ICD-10 code F7x), autism (ICD-10 code F84) or both, with at least 1 year of care under secondary mental healthcare services	People of any age with a recorded diagnosis of intellectual disability (ICD-10 code F7x), autism (ICD-10 code F84) or both, with at least 1 year of care under secondary mental healthcare services and an admission to a psychiatric inpatient ward for a period of at least 14 days
Intervention	Community C(E)TR	Community C(E)TR within 6 months prior to admission
Comparison	No community C(E)TR	Did not receive a community C(E)TR within 6 months prior to admission
Outcome		
Primary	Psychiatric hospital inpatient admission within 6 months of the community C(E)TR	Length of psychiatric hospital admission (days)
Secondary	Descriptive data and comparison of baseline demographics between intervention and comparison groups	Descriptive data and comparison of baseline demographics between intervention and comparison groups
	Descriptive data of 6 months pre-C(E)TR/post-C(E)TR (index date): neuropsychiatric symptoms, clinical variables and service use	Descriptive data and comparison of prehospital admission neuropsychiatric symptoms, HoNOS and service use Clinical and social functional improvement (change in HoNOS) while in hospital

C(E)TR, Care (Education) and Treatment Review; HoNOS, Health of the Nation Outcome Scales.

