### Inclusion and exclusion criteria

All eligible patients who were admitted to a psychiatric hospital for at least 14 days may be included in this study. We will exclude people who were not open to a SLaM community team for at least 6 months prior to their admission, as these people may have a high degree of missing data and may not have had an opportunity for a community C(E)TR before their admission or might represent new transfers from other NHS Trusts. We will also exclude ‘re-admissions’, defined as an admission occurring <6 months after the discharge date of a previous admission.

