#### Analysis of a 12-month horizon

We will re-run the analyses for both sub-studies across a 12-month horizon, to extend the results of the reported 6-month horizon and to capture potential impacts of community C(E)TRs across a longer time-frame.

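### Kaplan-Meier with deaths censored overstates the share discharged alive in sub-study 2; a cumulative incidence curve and a stated end of stay would correct it

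*Protocol article*

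**What the plan says.** Table 1 of the protocol article gives length of psychiatric hospital admission, in days, as the primary outcome of sub-study 2. The Time-to-event analysis section fixes the method:

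- Curve: "Time-to-discharge (length of hospital admission) will be analysed using the Kaplan-Meier estimator".
- Group comparison: "A Cox’s proportional hazards model will be used to estimate the HR for discharge", "for a follow-up period of 6 months after admission".
- Deaths: "Patients who die within 6 months of admission will be censored at the date of death".
- Stays still open: "patients who remain in hospital will be censored at the end of the 6 months".

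The section on the 12-month horizon extends this: "We will re-run the analyses for both sub-studies across a 12-month horizon". No competing-risk estimator is named, and no number of deaths or discharges is anticipated.

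**The concern.** Censoring tells Kaplan-Meier that the patient could still have the event later, at the same rate as those who remain under observation. That fits someone still in hospital at 6 months. It does not fit someone who has died there, for whom discharge is no longer possible. The section treats both alike.

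One minus Kaplan-Meier then describes discharge in a hypothetical setting where nobody dies in hospital, not the share of admitted patients who left alive. It is the only absolute time-to-event description the section names for this primary outcome. Each group's curve is shifted according to that group's own deaths, so a visual comparison of the curves would also be affected if deaths differed between the groups.

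The section also treats time to discharge and length of admission as one quantity. They differ for anyone who dies in hospital: the length of that admission is known, but the time to discharge does not exist.

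**Working it through.** The article states no figure that could be reproduced here, so the check compares the two estimators under stated assumptions.

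**From the article:** the event is discharge, deaths are censored, follow-up is 6 months, and the analyses are re-run at 12 months.

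**Assumed, not in the article:** constant daily hazards of discharge (*h_d*) and of death in hospital (*h_m*); Kaplan-Meier median stay of 60, 90 or 150 days, so *h_d* = ln 2 / median; *h_m* of 0.00005, 0.0001 or 0.0002 per day. The 14-day minimum stay for inclusion was not modelled.

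**Formulas at time T**

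- One minus Kaplan-Meier, deaths censored: 1 − exp(−*h_d*·T)
- Cumulative incidence of live discharge: *h_d*/(*h_d*+*h_m*) × [1 − exp(−(*h_d*+*h_m*)·T)]
- In-hospital deaths by T: the same expression with *h_m* in the numerator

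**Worked case:** median 90 days, *h_m* = 0.0002, T = 182 days. Here *h_d* = 0.693/90 = 0.00770 and *h_d*+*h_m* = 0.00790. One minus Kaplan-Meier is 75.4%; the cumulative incidence is 74.3%. The excess is 1.05 points, with 1.9% dying in hospital.

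**All cases at T = 182 days**

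| *h_m* per day | In-hospital deaths, medians 60 / 90 / 150 | Excess in share discharged (points) |
|---|---|---|
| 0.00005 | 0.4 / 0.5 / 0.6% | 0.27 / 0.26 / 0.22 |
| 0.0001 | 0.8 / 1.0 / 1.2% | 0.53 / 0.53 / 0.44 |
| 0.0002 | 1.5 / 1.9 / 2.4% | 1.06 / 1.05 / 0.88 |

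These percentages count deaths in hospital before discharge. They are not all-patient 6-month mortality, which at the same daily hazards, 1 − exp(−182·*h_m*), would be about 0.9%, 1.8% and 3.6%.

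**12-month re-run:** with the same hazards at T = 365 days the excess runs from 0.40 to 2.13 points.

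**If deaths were commoner:** with T = 182.5 days and medians of 45, 90 and 150 days, the excess is 0.7 to 1.6 points at 2% in-hospital deaths and 1.8 to 4.1 points at 5%.

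**Simulation:** 400,000 stays with a median of 90 days and 2% in-hospital deaths gave 75.5% by one minus Kaplan-Meier. Aalen-Johansen and the observed share were both 74.4%.

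**Length of stay, Kaplan-Meier median 90 days, T = 182.5 days**

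| Quantity | Kaplan-Meier | Correct value, 2% deaths | Correct value, 5% deaths |
|---|---|---|---|
| Median time to live discharge (the dead never discharged) | 90.0 | 91.1 | 92.9 |
| Median days in hospital, any exit | 90.0 | 87.6 | 84.2 |
| Mean days in hospital within 6 months, any exit | 98.0 | 96.6 | 94.4 |

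The any-exit median is ln 2/(*h_d*+*h_m*); the live-discharge median is the time at which the cumulative incidence reaches 50%. Kaplan-Meier falls between the two definitions and matches neither.

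**The case against.** The strongest reply is that the purpose of sub-study 2 is a comparison between groups, and that this is made with a Cox model. Censoring deaths is the standard way to obtain a cause-specific hazard ratio for discharge, so no estimate or test of the C(E)TR effect is shown to be wrong. That stands. A reader might infer that the primary comparison is invalid; the article does not support that. The only limit is that a cause-specific ratio does not by itself give the difference in the share discharged.

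A reader might also infer that the plan understates length of stay. That is true only for time to live discharge. Table 1 names the length of the admission, and if death ends it, censoring makes the Kaplan-Meier estimate too long.

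It can further be said that the article never promises to report the curve as a proportion discharged, that nothing in it suggests frequent deaths, and that supplementary curves and labels can be left to a fuller analysis plan. The point about size stands: at 1% in-hospital deaths or fewer, the excess was under 1 point in every scenario run. The other two carry less weight. A Kaplan-Meier curve of time to discharge will ordinarily be read as the share discharged by each day. The estimator and the censoring of deaths are also stated choices in the article, not details left open.

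**Conclusion.** The point holds as a minor improvement. The stated estimator is biased upwards for the share discharged alive whenever someone dies in hospital while others remain to be discharged. The likely size is about 0.2 to 1.1 percentage points at 6 months, and 0.4 to 2.1 at 12 months with the same hazards. These ranges rest on assumed death hazards, assumed median stays and constant hazards, because the article supplies none of these. The bias would matter more if in-hospital deaths were commoner or unequal between groups, and nothing in the article indicates either.

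The direction of any error in length of stay cannot be settled until the article says whether a stay ends at live discharge or at any exit. The Cox comparison is unaffected.

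**What to change.** In the Time-to-event analysis section:

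1. Replace the Kaplan-Meier curve with the Aalen-Johansen cumulative incidence of live discharge by group, with death in hospital as a competing event, at both 6 and 12 months.
2. State whether length of stay ends at live discharge or at any exit. If at any exit, count death as the end of the stay instead of censoring it when summarising days in hospital.
3. Keep the Cox model and label its result a cause-specific hazard ratio for discharge.
4. Report the number of in-hospital deaths in each group.

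The cost is a few sentences of wording. The date of death is already needed for the planned censoring, and R, which the article already names, has standard functions for this.

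Possible wording: *The probability of live discharge over time will be estimated in each group by the Aalen-Johansen method, with death in hospital as a competing event. The Cox model gives a cause-specific hazard ratio for live discharge. In-hospital deaths will be reported by group.*
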